## Abstract

**Background:**

Leading medical organizations have called on primary care pediatricians to take a central role in the prevention of childhood obesity. Weight counseling typically has not been incorporated into routine pediatric practice due to time and training constraints. Brief interventions with simple behavior change messages are needed to reach high-risk children, particularly Latino and Black children who are disproportionately affected by obesity and related comorbidities. Steps to Growing Up Healthy (Added Value) is a randomized controlled trial testing the efficacy of brief motivational counseling (BMC) delivered by primary care clinicians and the added value of supplementing BMC with monthly contact by community health workers (CHW) in the prevention/reversal of obesity in Latino and Black children ages 2-4 years old.

**Methods/Design:**

Mother-child dyads (targeted n = 150) are recruited for this 12-month randomized trial at an inner-city pediatric primary care clinic and randomized to: 1) BMC delivered by clinicians and nurses at well, sick, and WIC visits with the goal of reducing obesogenic behaviors (BMC); 2) BMC plus monthly phone calls by a CHW (BMC + Phone); or 3) BMC plus monthly home visits by a CHW (BMC + Home). During BMC, the medical team facilitates the selection of a specific goal (i.e., reduce sugar sweetened beverage consumption) that is meaningful to the mother and teaches the mother simple behavioral strategies. Monthly contacts with CHWs are designed to identify and overcome barriers to goal progress. Dyads are assessed at baseline and 12 months and the primary outcome is change in the child’s BMI percentile. We hypothesize that BMC + Phone and BMC + Home will produce greater reductions in BMI percentiles than BMC alone and that BMC + Home will produce greater reductions in BMI percentiles than BMC + Phone.

**Discussion:**

Steps to Growing Up Healthy will provide important information about whether a brief primary care-based intervention that utilizes a motivational interviewing and goal setting approach can be incorporated into routine care and is sufficient to prevent/reverse obesity in young children. The study will also explore whether monthly contact with a community health worker bridges the gap between the clinic and the community and is an effective strategy for promoting obesity prevention in high-risk families.

**Trial registration:**

ClinicalTrials.gov NCT01973153

## Background

Populations of color in the United States have disproportionately high rates of childhood obesity [1-3]. Obese children often become obese adults [4,5] setting the foundation for lifelong health disparities. Unfortunately, medical professionals and parents often fail to recognize obesity in young children and parents tend to minimize the risk that obesity poses to their child’s future health outcomes [6-10]. Latina and Black mothers commonly equate excessive weight with good health and interpret a body mass index (BMI) at the 97^th^ percentile or above as a desirable state [11,12]. When families do express interest in weight management, access to treatment is often limited to university-based clinics staffed by highly trained weight management specialists who are able to reach only a handful of children in need. Historically, these weight management programs focus on older children and those who are significantly obese, emphasizing obesity treatment rather than prevention. This model is an important component of obesity management but it is not sufficient. In light of the difficulty and expense of treating obesity once it has developed, widely available cost-effective obesity prevention approaches are needed to promote healthy lifestyles in very young children. Consistent with the Chronic Care Model [13,14], these programs should foster collaborations between health care systems and community resources and form partnerships with families to prevent obesity.

The primary care setting is an obvious context for addressing weight in very young children. Children see their health care provider for regularly scheduled well visits ~10 times before the age of 2 and yearly thereafter [15]. The primary care office thus could provide the continuity of care and frequency of contact needed for weight management in very young children; yet obesity is often not addressed at these visits [16]. O’Brien and colleagues [17] found that among obese children, obesity was documented in only 53% of charts, with diet and physical activity histories reported in only 69% and 15% of charts, respectively. Similar trends were recently reported in a large national sample of pediatricians, with only 55% reporting that they calculated children’s BMIs at well child visits [16]. Consequently, many parents are unaware of their child’s weight status [18] and receive no specific suggestions from their pediatrician regarding how to improve their child’s eating and exercise habits [19,20]. This is particularly true for children under 6 years, those who are overweight but not obese, and African-American, Hispanic, and Asian children [21]. Recognizing this missed opportunity, the American Academy of Pediatrics (AAP) recommends universal assessment of children for obesity risk by their primary care provider [22], a recommendation echoed by the Institute of Medicine’s 2012 report on accelerating progress in obesity prevention [23]. The 2007 AAP obesity guidelines outline a 15-minute obesity prevention protocol to improve early identification of elevated BMI, medical risks and unhealthy habits. These obesity prevention guidelines have not been widely adopted in the primary care setting. In part, this is because the average length of a well child visit is less than 20 minutes [24] and because clinicians often do not feel confident in counseling families about obesity or believe that counseling may not make a difference [20,25,26].

One intervention strategy that shows promise in establishing healthy lifestyles and could fit within the time constraints of primary care is motivational interviewing (MI) [27,28]. Using patient-centered strategies such as open-ended questions, positive affirmations and reflective listing, MI elicits internal motivation for behavior change while addressing the ambivalence and discrepancies between a person’s current values and behavior (e.g., “Heavy is healthy”) and their future goals (e.g., “I don’t want my child to get diabetes.”). This approach is ideal for primary care provider use because MI can be delivered in brief doses. Research has shown MI to be effective across a range of health behaviors, including diet and nutrition-focused interventions [29-31]. MI has been used successfully to supplement behaviorally-based adult weight loss programs and has been shown to have a positive impact after only 2 sessions [30]. In pediatric settings, MI has been associated with increased parent satisfaction and adherence and has been used in a nonrandomized childhood obesity prevention program [32]. More research is needed to test whether brief but recurrent doses of MI coupled with key behavioral strategies known to promote weight control (e.g., goal setting and self-monitoring) can be integrated into primary care to prevent childhood obesity and to explore how best to support the behavior change process outside of the clinic setting.

Community health workers (CHWs) bridge the gap between the primary care office and the community and may be a viable resource for reinforcing obesity prevention efforts once families leave the doctor’s office. CHWs are typically individuals from within a community who share many demographic similarities and life experiences with their target audience [33]. As a trusted member of a community, CHWs are able to offer culturally appropriate health education, counseling, and social support that can facilitate access to information and resources [34]. CHWs are being used extensively to address disease and case management, health information transfer, and health promotion and have been effective in promoting behavior change in multiple settings [35]. CHWs have had a positive influence on diabetes self-management [36] and breastfeeding outcomes [37] as well as on general nutrition knowledge and dietary intake behaviors among Latinos. A question that remains unanswered is whether CHWs can enhance obesity prevention outcomes above and beyond what can be achieved through primary care.

The present study is a randomized controlled trial designed to examine the efficacy of Steps to Growing Up Healthy, a primary care based obesity prevention program that utilizes a motivational interviewing framework and selected behavioral strategies to reduce obesogenic behaviors in Latino and Black children 2-4 years of age. The behavioral targets are reducing/eliminating sugar sweetened beverage consumption, changing the type and/or amount of milk consumed, decreasing screen time to less than 2 hours per day, and increasing physical activity to at least 60 minutes per day. The primary goal of this study is to examine whether repeated doses of brief motivational counseling delivered by primary care clinicians and nurses to mothers of young children are sufficient to prevent/reverse childhood obesity in this high risk group or if monthly contacts with a CHW via either telephone or home visits enhances any observed intervention effects. This project is innovative in that the initial obesity prevention activities are embedded in the context of routine clinic visits and are tested in combination with two modalities for providing CHW support. The study’s focus on preschool age children will also add to the small but growing literature on obesity prevention in this critical developmental window.

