## Methods/Design

### Overview and hypotheses

Latino and Black mother-child dyads (targeted *n* = 150) are recruited for this 12-month randomized trial at an urban based pediatric primary care clinic (Figure 1). Participating dyads are assigned with equal probability to one of three treatment conditions: 1) brief motivational counseling (BMC) alone delivered by the child’s medical team; 2) BMC plus monthly phone calls by a CHW (BMC + Phone); or 3) BMC plus monthly home visits by a CHW (BMC + Home). Dyads are assessed at baseline and 12 months. The primary outcome is change in the child’s BMI percentile. We hypothesize that over the 12-month period both BMC + Phone and BMC + Home will produce greater reductions in BMI percentiles than BMC and that BMC + Home will produce greater reductions in BMI percentiles than BMC + Phone. The study protocol was reviewed by the Scientific Review Committee at Connecticut Children’s Medical Center (CCMC) in Hartford, CT and received full approval by CCMC’s Institutional Review Board.

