##### BMC

All dyads in the study receive BMC delivered by clinicians and nurses at routine medical visits (well, sick, or WIC check-in) over a 12-month period. As part of standard care, every child in the primary care clinic is assigned to one of two teams consisting of attending clinicians, pediatric residents, nurses and medical assistants. Each child on the team is assigned to a “teamlet” (an attending clinician and nurse) who provides all of that child’s care [39,40]. Well child visits and the WIC visits are performed by the child’s teamlet while sick visits may be conducted by others on the child’s team. Any trained clinician or nurse seeing the family for any type of visit can offer the intervention. Each BMC dose is approximately 3-5 minutes long and incorporates basic MI strategies such as positive affirmations and reflective listening as well as behavioral elements including goal setting and contracting. Seven intervention steps guide this brief encounter (Table 1). First, in the waiting room, mothers complete a one-page survey created for this project (Steps to Growing Up Healthy Survey) regarding their child’s eating, physical activity, sedentary activity, and sleep habits (Step 1). At the start of BMC, the medical teamlet member quickly reviews the survey results with the family focusing first on areas of strength using a colorful circular diagram in English and Spanish (Step 2; Figure 2). The clinician then selectively focuses the mother’s attention on the four key behavioral targets that form the inner circle of the Steps to Growing Up Healthy circular diagram (Step 3). Using open-ended questions and reflective listening skills, the clinician and mother agree upon a behavior that the mother is ready and able to change (Step 4) and a plan of action specific for that child is agreed upon and documented in a written behavioral contract that clearly states the mother’s goal (Step 5; i.e., the Steps to Growing Up Healthy Action Plan). The clinician or nurse then offers the mother an educational handout containing suggestions for how to implement the desired behavior change (Step 6). The BMC dose ends with the clinician or nurse providing the mother with a monthly self-monitoring calendar that the mother can use to track goal progress via a simple yes/no daily checkbox (Step 7). At every visit during the next 12 months, the clinician and nurse are encouraged to use the Steps to Growing Up Healthy Survey and BMC with targeted communication to reinforce a previously agreed upon goal or to deliver a new behavior change message and set a new goal. In addition, within 5-7 days of each clinic visit, a member of the project staff conducts a brief (≤5 minutes) telephone call with the mother to review the visit, discuss initial implementation of behavior change and any problems encountered with the behavior change, and assess the fidelity of the intervention rendered by the medical teamlet according to the mother’s perception of the interaction.

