### Sample size and power

The primary outcome is change in child’s BMI percentile from baseline to 12 months. We hypothesize that both BMC + Phone and BMC + Home will reduce BMI percentiles compared to BMC. Assuming no change in BMI percentile for BMC and a 2.5 percentile change in BMI for BMC + Phone (i.e., 90^th%^ to 87.5^th%^) and a 5 percentile change in BMI in BMC + Home (i.e., 90^th%^ to 85^th%^), with an alpha of 0.05 and an ANCOVA with 3 treatment groups, we need 34 children per group to have 0.85 power to be able to perform 3 contrasts: BMC vs. BMC + Phone, BMC vs. BMC + Home, and BMC + Phone vs. BMC + Home. We plan to recruit 50 children per arm to allow for a 15% dropout rate. Even if 25% of participants drop out we will have 80% power to test our primary aims.

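### The BMC half of the stated aim (efficacy, and sufficiency to prevent or reverse obesity) has no randomised comparison behind it, because every arm receives BMC; the CHW half does

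*Protocol article*

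**What the plan says.** The aim appears in three places, each time with BMC as a question in its own right.

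- **Abstract, Background:** the trial is described as "testing the efficacy of brief motivational counseling (BMC) delivered by primary care clinicians and the added value of supplementing BMC with monthly contact" by CHWs. Efficacy of BMC and added value of CHW contact are two separate items.
- **Abstract, Discussion:** the trial is expected to inform whether the brief primary care intervention "is sufficient to prevent/reverse obesity in young children".
- **Background, last paragraph:** "The primary goal of this study is to examine whether repeated doses of brief motivational counseling delivered by primary care clinicians and nurses" are sufficient, "or if monthly contacts with a CHW via either telephone or home visits enhances any observed intervention effects". This is an either/or, with a BMC half and a CHW half.

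The design is set out under Methods/Design.

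- **Overview and hypotheses:** "Participating dyads are assigned with equal probability to one of three treatment conditions", namely BMC, BMC + Phone and BMC + Home. The hypotheses rank these three arms against each other.
- **BMC:** "All dyads in the study receive BMC delivered by clinicians and nurses at routine medical visits".
- **Sample size and power:** three pairwise contrasts among the same arms. The planning values begin "Assuming no change in BMI percentile for BMC", with changes of 2.5 points for BMC + Phone and 5 points for BMC + Home.
- **Primary analysis:** the between-subjects factor has these three levels. Chart-review heights and weights are used to impute missing change.
- **Secondary analyses:** 12-month BMI percentile is regressed on the number of intervention doses received, adjusted for baseline.

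**The concern.** A randomised trial supports a causal statement about what differs between its arms. BMC does not differ between these arms. The aim statements nevertheless announce a randomised test of BMC and an answer on its sufficiency.

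What is at stake is the conclusion. If the aim stands as written, a BMC arm whose percentile stays flat or falls, or three arms that end up alike, could be presented as an answer to the question of sufficiency, with the authority of a randomised trial. Neither result would carry that meaning. The analysis plan cannot repair this, because no analysis creates a comparison group that was never allocated.

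**Working it through.** **Inputs**

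- Arms: three with equal allocation; 3 x 50 = 150 dyads (Overview and hypotheses; Sample size and power).
- Arms without BMC: none (BMC section), so 0 of 150 dyads are allocated to no BMC.
- Planned changes in BMI percentile: 0, -2.5 and -5 (Sample size and power).
- Contrasts: BMC + Phone against BMC, BMC + Home against BMC, BMC + Home against BMC + Phone.

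The article's 34 children per group does not enter this argument. It gives no standard deviation, so that figure can be neither confirmed nor refuted from the text.

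**Step 1: what each arm estimates.** Let d be the 12-month change that would occur without the programme, b the effect of the BMC package, and p and h the further effects of phone and home contact on top of BMC. The expected changes are:

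- BMC: d + b
- BMC + Phone: d + b + p
- BMC + Home: d + b + h

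**Step 2: what each contrast estimates.**

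- (d + b + p) - (d + b) = p; planned value -2.5 - 0 = -2.5
- (d + b + h) - (d + b) = h; planned value -5 - 0 = -5
- (d + b + h) - (d + b + p) = h - p; planned value -5 - (-2.5) = -2.5

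The term b appears in none of them. If CHW contact works partly by making BMC more effective, that gain falls into p and h, and b is still not isolated.

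**Step 3: what a flat BMC arm means.** The planning value is d + b = 0. Using 2.5 points purely as an illustration, this holds equally for:

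- d = 0, b = 0: BMC is inert;
- d = +2.5, b = -2.5: BMC prevents a rise;
- d = -2.5, b = +2.5: BMC blunts a fall.

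With the planned p and h, all three give the same expected changes of 0, -2.5 and -5. The data cannot tell them apart.

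**Step 4: what no difference between arms means.** Then p = h = 0. This says nothing about b: BMC may be enough alone, or all three programmes may be equally without effect.

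**Step 5: the other planned analyses.**

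- The time effect in the repeated measures model, averaged over equal arms, estimates d + b + (p + h)/3. It is a before-after quantity and still contains d.
- The dose regression uses an exposure that is not randomised. BMC doses depend on clinic attendance and on whether staff deliver them. By plan, every dyad has its first dose at the enrolment visit (Recruitment and randomization), so a no-dose group is essentially absent. If CHW contacts are counted as doses, the randomised part of the variation concerns CHW contact, not BMC.
- Chart-review data are planned for imputation only, not as a historical comparator.

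**Step 6: what d contains.** The outcome is an age- and sex-specific percentile (Height and weight), so normal growth is already referenced out. Trends in the clinic or population, volunteer effects and regression to the mean are not.

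**The case against.** The strongest reply is that this is an add-on trial and its working parts treat it as one. The study name carries the label Added Value. The hypotheses, contrasts, power statement and group factor all concern CHW contact. No hypothesis says that BMC lowers BMI percentile, and no single-arm test of BMC is planned. Leaving out a usual-care arm is legitimate for that question. The Background sentence can also be read narrowly: is BMC enough, or does CHW contact add to it?

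Much of this stands. A reader might infer that the whole primary goal is unanswerable. The documents do not support that, because the CHW half is addressed directly by the randomised contrasts. Three further inferences also go too far:

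- That the before-after change is the only evidence on BMC. A dose-response regression is planned as well, although it is not randomised.
- That the planning value of no change in the BMC arm concedes failure. It is a reference point for differences between arms, and for prevention a flat percentile need not be a bad result.
- That the project-staff calls after clinic visits contaminate the BMC arm. They are described within the BMC package common to all arms.

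The reply does not cover the abstract. There, efficacy of BMC is listed apart from the added value of CHW contact, and sufficiency is named as something the trial will inform. Even on the narrow reading, failing to find a CHW benefit does not establish that BMC works.

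**Conclusion.** The point holds for the BMC half of the aim. No randomised comparison bears on the efficacy or sufficiency of BMC, and the supporting figure is 0 of 150 dyads allocated to no BMC. This follows from the stated arms and contrasts and needs no assumption about variance, dropout or effect size. The CHW half of the aim is answerable as designed.

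A reader might want to attach a precision or a probability of a misleading result to the BMC-arm change. The documents do not allow it. No standard deviation is given. Solving back from 34 per group and 0.85 power with two-sided tests gives values from about 3.0 to 6.9 points, depending on which test the power refers to. Those would be ANCOVA residual standard deviations, not the change-score standard deviation that a before-after interval needs. No size of background drift is given either. Precision is in any case beside the point, because a narrow interval around d + b still does not separate d from b.

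The stated aim needs correcting because it promises a causal conclusion that the design cannot deliver.

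**What to change.** Reword the aim in the abstract (Background and Discussion) and in the last paragraph of the Background. State the randomised question as whether adding monthly CHW phone calls or home visits to BMC lowers the child's BMI percentile at 12 months more than BMC alone, and whether home visits do so more than calls. Bring the matching efficacy sentence in the main Discussion into line.

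Drop efficacy of BMC and sufficiency of BMC as trial conclusions. Label the BMC-arm 12-month change and the dose-response regression as descriptive and non-randomised. State that neither a flat BMC arm nor an absence of difference between arms will be read as showing that BMC is sufficient.

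The cost is a narrower headline claim. Randomisation, contrasts, sample size and primary model are unchanged. Keeping the efficacy claim would instead require a concurrent group without BMC, which would be a different trial.

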## Methods/Design

### Overview and hypotheses

Latino and Black mother-child dyads (targeted *n* = 150) are recruited for this 12-month randomized trial at an urban based pediatric primary care clinic (Figure 1). Participating dyads are assigned with equal probability to one of three treatment conditions: 1) brief motivational counseling (BMC) alone delivered by the child’s medical team; 2) BMC plus monthly phone calls by a CHW (BMC + Phone); or 3) BMC plus monthly home visits by a CHW (BMC + Home). Dyads are assessed at baseline and 12 months. The primary outcome is change in the child’s BMI percentile. We hypothesize that over the 12-month period both BMC + Phone and BMC + Home will produce greater reductions in BMI percentiles than BMC and that BMC + Home will produce greater reductions in BMI percentiles than BMC + Phone. The study protocol was reviewed by the Scientific Review Committee at Connecticut Children’s Medical Center (CCMC) in Hartford, CT and received full approval by CCMC’s Institutional Review Board.

